# European Cohorts of patients and schools to Advance Response to Epidemics (EuCARE): a cluster randomised interventional and observational study protocol to investigate the relationship between schools and SARS-CoV-2 infection

**DOI:** 10.1186/s12879-022-07947-6

**Published:** 2023-01-03

**Keywords:** Schools, Pandemic, COVID-19, Children’s health, Adolescents’ health

## Abstract

**Background:**

Contradictory results were reported on the role of school closure/reopening on the overall SARS-CoV-2 transmission rate, as well as on which kind and level of mitigation measures implemented in schools may be effective in limiting its diffusion. Some recent studies were reassuring, showing that opening did not increase the community spread, although teachers and families are worried about the high class density. On the other hand, distance learning was associated with a negative impact on learning, sociability and psychological health, especially in vulnerable children. As it becomes clear that the SARS-CoV-2 pandemic will last for a long time, there is a high need for studies and solutions to support safe schools opening based on scientific evidence of harms and benefits. The Lolli-Methode (LM) is a strategy for epidemiological surveillance and early intervention aiming at SARS-CoV-2 outbreaks’ reduction in schools, relying on polymerase chain reaction analysis of saliva samples.

**Methods:**

In this cluster randomised trial protocol, we aim to determine whether the LM is useful to support schools opening and to reduce clusters and attack rates in schools, compared with the standard of care (SoC) surveillance by public health departments. This multicenter study will enrol 440 classes (around 8800 students, teachers and other personnel) from two countries, cluster randomised to LM or SoC. The samples from the pools will be collected and tested using PCR-based techniques. Test results will be combined with questionnaires filled in by children, parents, schoolteachers, and principals, concerning ongoing mitigation measures, their perceived psychological impact and other health and socio-economic information. An ancillary observational study will be carried out to study the prevalence of SARS-CoV-2 in schools, frequencies and size of clusters and attack rates, to compare the effectiveness of the different preventive measures adopted and to evaluate psychological issues in students and teachers in relation to the pandemic’s containment measures.

**Discussion:**

By the end of this study, we will have defined and characterised the applicability of the LM for SARS-CoV-2 surveillance, as well as the impact of pandemic preventive measures on children and teachers.

*Trial registration* International Standard Randomised Controlled Trial Number: NCT05396040, 27.05.2022*.*

**Supplementary Information:**

The online version contains supplementary material available at 10.1186/s12879-022-07947-6.

## Background and rationale

School closures represent a widespread non-pharmacological intervention (NPI) in the context of the current COVID-19 pandemic. The rationale for such a NPI has mostly been drawn from the reported beneficial effect of school closure during influenza pandemics. However, the COVID-19 disease spread and virulence by age have soon proved to be very different from those of influenza, with less frequent infections and milder manifestations in children than in adults [1–4]. Also, several studies showed that, when appropriate mitigation measures are implemented, the prevalence of positive cases in schools is lower than in the general population and the number and size of clusters are smaller [5–11].

This is indeed what emerged also from our cross-sectional and prospective cohort study in Italy, one of the European countries with the highest SARS-CoV-2 incidence, during the second COVID-19 wave (from September 30, 2020, until February 28, 2021) [12] on 7976 public school institutes (97% of total), accounting for 7,376,698 students, 775,451 teachers and 206,120 non-teaching staff members. The analysis also evidenced that school opening was not related to the second COVID-19 wave in Italy.

On the other hand, the recent epidemic variants Delta and Omicron, in combination with the low vaccine coverage of children, resulted in a significant increase of cases in children from 0 to 17 years of age, especially in the groups 0–6 and 14–17 years old. Some modelling studies showed a relevant effect of school closure/reopening on the overall transmission rate depending also on the impact on the overall mobility, although the authors underlined that their studies were not able to disentangle the results by the kind and level of mitigation measures implemented in the schools [13, 14]. Furthermore, there is little evidence and even less agreement on which mitigation measures are more efficient and as to what level of mitigation is needed [15, 16].

Most schools of all grades have been kept closed in many countries, preventing in-person learning and consequently generating an acute debate in society and science, which is still one of the most contentious issues of the COVID-19 pandemic. The spread of lineage Variant Of Concern (VOC) B.1.1.7 has worsened the fears and caused further schools’ closure in the UK and in Europe [17–20].

Importantly, school closure, supported or not by remote teaching, has been proven to cause harms to children and society in terms of health [21], psychological consequences [22, 23] and learning deprivation [24] with consequent long-term learning losses [25, 26], that are higher in socio-economically disadvantaged individuals [27] and that many consider to outweigh the benefits [19].

There is a high need for studies and solutions to support safe schools opening during a pandemic based on scientific evidence of harms and benefits. This means for instance to establish affordable and reliable surveillance systems to evaluate the prevalence, attack rates and clusters of SARS-CoV-2 in schools in relation to VOCs, to assess the best preventive measures to be adopted in schools in relation to VOCs, to disentangle the effects of school attendance (including related mobility) on the transmission rate of SARS-CoV-2 in the society as well as to evaluate the psychological health and learning damages associated to schools closure.

### The Lolli-Methode

Molecular salivary testing for the early detection of SARS-CoV-2 infection has proven to be a reliable tool for active surveillance and its use in communities has been reported [28]. The Institute of Virology at UniKoeln has implemented its use and developed a non-invasive SARS-CoV-2 screening method and intervention strategy based on saliva pool testing, namely “The Lolli-Methode” (LM) (exported with the name “Lolli Strategy” in Mexico) [29].

LM relies on saliva self-sampling by participants (adults and children, including babies) who need to suckle a swab as if it was a lollipop, for 30 s. Its application in schools implies that the swabs are pooled in defined groups, such as all the pupils and teachers of a class. Each pool/class is analysed collectively by a single PCR test. Negative pools imply no further action is needed. In case of a positive pool, all the individuals included in the group will have to collect again their saliva that, at this time, will be analysed individually.

The sampling/testing is meant to be performed twice a week, to allow early infection detection, competing with the time required by contact tracing protocols for the identification of positive cases and epidemiological surveillance purposes. Assuming a low positive rate in schools, this methodology is significantly more affordable in terms of logistics and costs with respect to separate analysis of individual swabs.

The sensitivity of LM was evaluated and found comparable with throat swabs plus nasopharynx swabs, both comparing single LM sample against swab and comparing single LM samples against pooled ones [29].

LM was introduced in pilot programs for children in kindergartens (“Kiko”) and schools, “B-FAST” [30], and “SCHOCO”, and extended, in collaboration with the Department of Health and the Department for Children, Youth and Family of the City of Cologne, in 32 kindergartens and 20 schools of Cologne.

LM was subsequently further extended to all the kindergartens (690) in Cologne, 130 kindergartens in Düren, and in North-Rhine-Westphalia state were included 95 kindergartens and all the schools (3700). In Mexico, the program has been successfully implemented as a pilot project in 394 schools and kindergartens of the Mexican state of Tabasco. Such accomplishments prove that LM can be adopted in different territories, populations, and conditions.

The LM design is intended to facilitate the implementation in any laboratory; therefore, any standard commercially available laboratory material can be used. The needed materials are: (i) swabs for sample collection, (ii) 50 ml capacity tubes for collecting the swabs in pools, and (iii) PBS or saline solution to hydrate the collected pool. In case that the recommended material (swabs, tubes) are not available, the material can be replaced by other commercial swabs or tubes which are equivalent. Standard material, namely Lolli-QM is available to verify the usability.

Specific indications on the materials and procedures are reported in the Additional file 1.

In the pilot phase in Cologne, 11 positive cases were detected in 32 kindergartens over a period of six weeks. The implementation in North-Rhine-Westphalia was conducted for 23 weeks with 2 vacation periods of 6 and 2 weeks, respectively, testing 742,771 individuals twice per week. The positivity rates were higher directly after vacation and were decreasing progressively after Lolli implementation [29]. The positivity rate at week 19 was 0.46%, reducing to 0.05% on week 26. After summer holidays we found 2.61% positivity rate at week 33 reducing to 0.92% three weeks later [29]. LM was implemented on a voluntary basis and acceptance resulted in more than 90%. No accidents or harm to any participant were reported or detected.

Comparator is the SoC, usually consisting in contact tracing activity performed by public health departments and routine surveillance based on symptoms prompting testing during large waves of the epidemic. It’s worth mentioning that SoC may undergo changes along the study, given that public health surveillance guidelines have been changing frequently along the pandemic.

The benefit/risk ratio for participants is very high, as there are potentially no risks coming from the performed tests. In fact, LM testing is well established and safe to perform. Moreover, it is less invasive than nasopharyngeal swabs and easily accepted by children. The benefits of this study consist in the possibility to find a more effective way to control the spread of the infection in schools compared to SoC and at the end reduce the number of days in distant learning. Furthermore, it contributes to provide a better understanding of the COVID-19 epidemics in the school setting.

## Study design

### Study objectives

#### Overall objective

The project represents a multidisciplinary interconnected effort to provide robust, data driven evidence to deal with SARS-CoV-2 variants and COVID-19 epidemics in the school setting, by comparing testing and containment strategies in different countries. Here we present the protocol version 1.1 from the 24.02.2022.

#### Primary objective

The primary objective is:To determine if regular screening with pooled saliva tests by LM is useful to support school opening and to reduce clusters and attack rates in schools, compared with SoC contact tracing by public health departments and surveillance based on symptoms prompting testing.

#### Secondary objectives

The secondary objectives are:To determine the incidence and prevalence of SARS-CoV-2, as well as clusters’ frequencies and size and attack rates in schools with the new variants, compared with the same indexes observed in the previous waves.To verify whether positive cases at school were caused by transmission within the school.To compare the effectiveness of different preventive measures adopted in different schools taking into account variants and vaccination (including social distance, wearing masks, preventive measures during lunch time, use of bubbles, extra-scholar activities).To compare the efficacy of different protocols of contact tracing in controlling clusters and attack rates and rates of quarantines.To investigate the potential psychological impact of the use of molecular saliva tests, different preventive measures and distant learning during schools' closures or quarantines in students, teachers and other school personnel, taking into account their socio-economic status and the household composition (single parent, presence of elderly in the house, etc.).To investigate differences in SARS-CoV-2 incidence by socio-economic status and distance from school/mobility issues.To investigate household secondary transmission attack rates.To evaluate schools usefulness as sentinel testing sites for community detection and control of SARS-CoV-2 epidemics.

### Study outcomes

#### Cluster randomised interventional study

##### Primary outcomes

Frequencies of clusters in classrooms in which pooled saliva tests (LM) are performed in association with standard contact tracing protocols, compared with classrooms in which SoC only protocols are applied.Number of classes and of students in the classes that accept to participate in the LM study, if asked, during time.

##### Secondary outcomes

Transmission/prevalence of SARS-CoV-2 in schools by variants, by assessing the proportion of students/staff with positive SARS-CoV-2 test identified by pooled saliva tests (LM).Size of clusters and attack rates in classrooms in which pooled saliva tests (LM) are performed, compared with classrooms in which standard contact tracing protocols is applied.Number/size of clusters associated with the use of different preventive measures in different classrooms, by prevalence of different variants and taking into account vaccination rates.Number of students participating in the project per class across time.Proportion of classes who accept to participate in the LM.Psychological status of students (in terms of emotional and behavioural problems) and school staff (in terms of of psychologcal well-being) through standardized questionnaires and ad hoc questions, from kindergarten to high school during the COVID-19 pandemic with respect to the use of LM and other preventive measures such as face masks, social distancing, distance learning, vaccines, etc., as well as attitude toward vaccinated and non-vaccinated students.Household secondary attack rate and dynamics of infections in terms of school imported or house imported, extending the LM to the household members of positive school cases.Social and mobility outcomes in terms of mobility changes and social interaction/distancing changes during the different waves will be analysed through statistical analyses and spatio-temporal analyses.

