### Statistical methods

#### Hypothesis

The main hypothesis is that the LM can reduce the frequency of clusters (i.e. two or more cases in a class within a scholar week).

The main endpoint is the frequency of cluster per class in a scholar week.

Secondary endpoints are cluster size and duration of consecutive/serial infections in the same class.

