#### Determination of sample size

Clusters are defined as epidemiologic links between an index patient and one or more persons who likely acquired SARS-CoV-2 infection in class (i.e., class-associated cases). Given the average infection rates in contacts of about 4% per class [31], a sample size of 440 classes (220 per arm) achieves 80% power to detect a difference between the group proportions of 3.5%. The proportion in arm with LM is assumed to be 4% under the null hypothesis and 0.05% under the alternative hypothesis. The test statistic used is the one-sided Z test with pooled variance with a 5% significance level.

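### Cluster size exists only where a cluster occurred, so comparing it between arms is not protected by randomisation and can miss or reverse a true reduction in cases

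*Protocol article*

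**What the plan says.** Under the interventional study's Secondary outcomes, the article lists "Size of clusters and attack rates in classrooms in which pooled saliva tests (LM) are performed", set against classrooms under standard contact tracing. Assessment of secondary outcomes repeats that LM and SoC will be compared on both measures. General study design makes the dimension of clusters part of what the two groups of classes are compared on.

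In Statistical methods, Hypothesis, a cluster is "two or more cases in a class within a scholar week", and the main hypothesis is that LM lowers the frequency of clusters. "The main endpoint is the frequency of cluster per class in a scholar week". The same section adds: "Secondary endpoints are cluster size and duration of consecutive/serial infections in the same class".

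Determination of sample size describes a cluster as an index patient linked to at least one further person probably infected in class. On that wording, too, the smallest cluster has two cases.

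The article states no analysis set, scoring rule or test for cluster size by arm.

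**The concern.** Randomisation makes the two sets of classes comparable. It does not make comparable the two sets of clusters that later arise in them. Size is undefined in a class-week with fewer than two cases, and LM is meant to move class-weeks into that state. A comparison of size between arms therefore conditions on a post-randomisation event that the intervention affects. This would remain even if every infection were detected in both arms, so it is separate from the difference between screening and symptom-prompted testing.

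The threshold of two makes the selection plausible. If LM isolates an index case early, a cluster of two becomes a single case. That success removes a small cluster from the LM arm's size data and raises the mean size of those left. The size comparison could then be null or unfavourable while LM truly reduces cases, and a reader could take it as evidence that LM does not limit spread once infection has entered a class.

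**Working it through.** **1. Selection, by definition.** Let Y be the number of cases in a class-week. A cluster exists if Y ≥ 2, and its size is Y given Y ≥ 2. The size contrast is E(Y | Y ≥ 2, LM) against E(Y | Y ≥ 2, SoC). The main hypothesis is that P(Y ≥ 2) differs by arm, so the conditioning sets differ by arm. E(Y), taken over all class-weeks with zeros included, has no such condition.

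**2. What the size contrast can show.** Both examples are hypothetical, since the article gives no distribution of cluster sizes.

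- Prevention unrelated to size: clusters fall from 4% to 0.5%, a reduction of (4 − 0.5)/4 = 87.5%. The remaining clusters have the same mean size, so the ratio is 1.0.
- Prevention mainly of small clusters: SoC has six clusters of size 2 and three of size 5, which is 12 + 15 = 27 cases and a mean of 27/9 = 3.0. LM leaves one cluster of size 5, mean 5.0. The size ratio is 5.0/3.0 = 1.67 against LM. Cases in clusters fall by (27 − 5)/27 = 81%. If each of the eight prevented clusters still leaves one isolated case, total cases are 5 + 8 = 13, a fall of (27 − 13)/27 = 52%. Multiplying all counts by a constant leaves these ratios unchanged, so the reversal does not come from small numbers.

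**3. The plan's own sample size.** Inputs from Determination of sample size: 220 classes in each arm, power of 80%, a detectable difference of 3.5 percentage points, and a pooled-variance Z test, one-sided at 5%. On the rates, that section states: "The proportion in arm with LM is assumed to be 4% under the null hypothesis and 0.05% under the alternative hypothesis". Formula per arm, with p̄ the mean of p₁ and p₂:

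n = [1.645·√(2p̄(1−p̄)) + 0.842·√(p₁(1−p₁) + p₂(1−p₂))]² / (p₁−p₂)²

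- 4% against 0.5%, which fits the stated difference of 3.5 points: n = 221 per arm, and power at 220 is 79.8%. The plan's figure reproduces.
- 4% against the printed 0.05%, a difference of 3.95 points: n = 157 per arm, and power at 220 is 90.5%. It does not reproduce.

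**4. How many clusters there would be.** Expected number = classes × proportion, or classes × weeks × proportion. The number of school weeks in the six months is not given; 20 to 26 is assumed.

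| Reading | SoC | LM |
|---|---|---|
| One observation per class, LM 0.5% | 220 × 0.04 = 8.8 | 220 × 0.005 = 1.1 |
| One observation per class, LM 0.05% as printed | 8.8 | 220 × 0.0005 = 0.11 |
| Per class-week, LM 0.5% | 176 to 229 | 22 to 29 |
| Per class-week, LM 0.05% | 176 to 229 | 2.2 to 2.9 |

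The 4% is itself a weak basis for any of these counts, because the article introduces it with "Given the average infection rates in contacts of about 4% per class", an infection rate among contacts and not a share of classes with a cluster.

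**The case against.** **The restriction is not printed.** The article nowhere says that size is compared only where a cluster occurred, and an analysis plan that is not shown could score zero elsewhere. It is true that the restriction is implied and not stated. But it follows from the definition: scoring zero where there is no cluster would replace the size of clusters with a different endpoint, so this is more than a detail left open.

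**Prevented clusters are still counted.** They enter the main endpoint, cluster frequency per class and week. This stands: the problem concerns one secondary comparison and leaves the main endpoint untouched. A size ratio of 1.0 would also be a correct description of the remaining clusters; the error lies in reading it as an effect of LM.

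A reader might also infer more than the documents support:

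- **That the comparison would rest on about nine clusters against one.** This needs 0.5% in place of the printed 0.05%, and one observation per class, whereas the main endpoint is per class-week. Per class-week at 0.5% the clusters are not scarce. Scarcity therefore cannot carry the point.
- **That duration of serial infections has the same flaw.** The article ties duration to consecutive infections in the same class. Single cases in successive weeks could qualify without any cluster.
- **That attack rates are conditional too.** Nothing printed limits their denominator to classes with a cluster.

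**Conclusion.** The point holds for cluster size. As defined in the Hypothesis section, it has a value only in class-weeks with two or more cases, and LM is hypothesised to change how often that happens. The between-arm size comparison is therefore not a comparison of the randomised groups. It could show no effect, or an effect in the wrong direction, when LM reduces cases.

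This rests on the definition and the hypothesis alone, not on any assumed rate. The size of the distortion cannot be derived from the article; the ratios of 1.0 and 1.67 show what is possible and are not forecasts. The expected number of clusters is not unique either, and cannot be stated until the 0.05% is reconciled with the 3.5-point difference, and the per-class proportion with the per-class-week endpoint. The criticism does not extend to the main endpoint, to attack rates or to duration.

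**What to change.** - Make the secondary between-arm comparison the number of cases per class over all randomised classes, with zeros included.
- Alongside it, use the attack rate that is already listed, with all enrolled class members as the denominator. Enrolled members are preferable to the full class roster because infection status may not be collected for pupils who did not consent.
- Analyse both by allocated arm, using a count model (negative binomial, or Poisson with cluster-robust errors) with an offset for the number enrolled, allowing for repeated weeks within a class and for clustering.
- Report cluster size given a cluster as description only, with the number of clusters in each arm beside it.

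The cost is small: a change of wording and of model. Cases in enrolled members are already needed to identify clusters, and the section on missing data and drop-outs already plans to record the number enrolled per class each week. Counting all cases also avoids having to attribute each one to transmission in class.

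The change does not remove unequal case detection. LM classes are screened twice a week while SoC classes rely on symptoms and contact tracing, so more of the infections that occur may be found under LM. The plan should state this as a limitation of the new comparison as well.
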